# A quasi-experimental mixed-method pilot study to check the efficacy of the “SOUND” active and passive music-based intervention on mental wellbeing and residual cognition of older people with dementia and dementia professionals’ burnout: a research protocol

**DOI:** 10.3389/fpsyg.2024.1327272

**Published:** 2024-02-14

**Keywords:** music, dementia, non-pharmacological intervention, well-being, cognitive function

## Abstract

**Purpose:**

The SOUND method offers an innovative blended intervention based on music circle-activities and cognitive stimulation approaches which was co-designed by musicians, health professionals, older people with dementia, family caregivers and researchers, for its application in dementia settings. The purpose of the paper is to describe the detailed procedure of the quasi-experimental pilot study.

**Method:**

The experimental phase of SOUND uses a mixed-method design encompassing qualitative and quantitative observations, cognitive testing, self-report and interviewer-assisted questionnaires to investigate the effectiveness of the intervention for 45 people with dementia and 45 professionals (15 in every study country: Italy, Portugal, Romania).

**Results:**

The pilot study will be the first implementation of the SOUND intervention aiming to investigate the feasibility and preliminary effects of the method.

**Conclusion:**

The novelty of SOUND is its multicomponent method, including the most evidenced features for improving the wellbeing of participants.

## 1 Introduction

Dementia is an umbrella term to describe a set of cognitive, psychological and behavioral symptoms caused by brain diseases or conditions which are often progressive and non-reversible. The most common form of dementia, 60–70% of cases, is Alzheimer’s disease. Dementia is mostly prevalent in older age, with a significant increase over time as it almost doubles every 5 years after the age of 65 (World Health Organization, 2021). It is estimated that over 55 million of people live with dementia worldwide of which 9.780.678 in Europe (Alzheimer Europe, 2019; World Health Organization, 2021). This global epidemic is expected to almost triple by 2050 because of population ageing particularly in low and middle-income countries (World Health Organization, 2021).

There is no cure for dementia, although certain pharmacological treatments may slow down the progression of the disease. Nevertheless, evidence shows that pharmacological therapies for treating the psychological and behavioral symptoms of dementia (BPSD) have limited efficacy, severe adverse effects and increased mortality. Consequently, it is recommended to use non-pharmacological treatments (NPT) as a first-choice intervention (Magierski et al., 2020; Carrarini et al., 2021). In fact, NPT can be complementary treatments as, with a minimal risk for adverse effects, they can prevent and reduce BPSD, endorse quality of life, improve or maintain cognition and positively change brain activity (Dyer et al., 2017; Chalfont et al., 2018; Shigihara et al., 2020). A range of NPT are available, such as socio and psycho-educational approaches, cognitive and emotion interventions, physical exercise and sensorial activities (e.g., music, art and massage therapies). Other psychoeducational interventions are linked to training professionals and informal caregivers in order to reduce their stress/burnout and to improve their knowledge on dementia care (Barbosa et al., 2014; Briones-Peralta et al., 2020). Among all, music interventions targeted to older people with dementia seem to be the most effective NPT to manage BPSD (Abraha et al., 2017; Dyer et al., 2017). Indeed, music is associated to mental wellbeing, quality of life, self-awareness and coping in people with diagnosed health conditions and to reduced risk of depression in older people (Daykin et al., 2017). Moreover, music training looks like a powerful means for preventing the neurocognitive degeneration, since music enhances cerebral plasticity and induces the creation of new connections in the brain (Hyde et al., 2009; Habibi et al., 2017).

Musical leisure activities seem to have a positive effect on the cognitive, emotional, and neural function of older people both during normal aging (Klimova et al., 2017; Särkämö, 2018) and with dementia (Särkämö, 2018). Considering the latter, music can improve various aspects of their health and well-being: (a) cognition, especially verbal fluency and attention; (b) psychological aspects, such as mood, sense of self and identity; (c) mobility and coordination; (d) and behavior by reducing agitation, buffering isolation and strengthening communication (Brancatisano et al., 2019). Some studies show that music interventions can improve the cognitive state (Moreno-Morales et al., 2020), attention, immediate and delayed memory, executive function and gait speed (e.g., Domínguez-Chávez et al., 2019).

There is a great variety of music interventions including for instance, listening to music, playing instruments, and singing in chorus, but it is still not clear which is the most effective type of intervention and what are the factors determining their effectiveness. A relatively recent systematic review (Moreno-Morales et al., 2020) underlines that interventions involving listening to music have a greater positive effect on cognitive functions compared to active musical activities, such as singing or playing an instrument. In fact, listening to music implies a wide cortical activation by requiring the integration of perception of sounds, rhythms, and lyrics, alongside the simultaneous attention to the environment (Gaser and Schlaug, 2003; Soria-Urios et al., 2011; McDermott et al., 2012).

Many interventions, for example, are based on music therapy, i.e., an evidence-based practice carried out by trained and certified music therapists. Music therapy treatments can improve cognition (Bruer et al., 2007; Chu et al., 2013) and verbal fluency (Brotons and Koger, 2000; Lyu et al., 2018) whilst they can reduce associated symptoms of dementia such as depression (Chu et al., 2013) and agitation (Lin et al., 2010; Raglio et al., 2010; Vink et al., 2012; Tsoi et al., 2018). Music therapy can also have positive effects on clinical parameters by decreasing the systolic blood pressure of older people living in nursing home (Uğur et al., 2016).

Furthermore, group music-based treatments, i.e., based on passive and active music making exercises, not necessarily music therapy driven, can also reduce apathy (Tang et al., 2018), agitation (Choi et al., 2009; Ho et al., 2018) and depression (Ashida, 2000) and improve overall cognition (Cheung et al., 2016; Tang et al., 2018), verbal fluency and memory (Cheung et al., 2016). Thomas et al. (2017) demonstrated that individualized music treatments, such as personalized playlists, can have a positive effect on individuals’ mental health by reducing the use of antipsychotic medication with people with dementia.

Nevertheless, there is no agreement in the literature around the effectiveness of music-based intervention in different realms among older people with dementia, as research is still in initial stages. For example, Van der Steen et al. (2017) underlines that there is no evidence that music-based therapeutic interventions have effects on agitation or aggression, on emotional well-being or quality of life, nor on behavioral problems. Conversely, Moreno-Morales et al. (2020) conclude that there is evidence that music therapy can improve cognitive function in people living with dementia, that it can have a positive effect in the treatment of long-term depression and it can improve quality of life of people with dementia in the short-term.

The lack of evidence around the effectiveness of music interventions with OPDs, may depend on the studies small sample size, unclear assessment methods, the variety of music interventions (Van der Steen et al., 2017) and of tests used for the outcomes assessment (Moreno-Morales et al., 2020) and the absolute dearth of longitudinal studies that can demonstrate the long-term effect of music interventions on OPDs’ mood, cognitive and physical function (Moreno-Morales et al., 2020).

Non-pharmacological treatments, including music-based intervention, can have a positive effect also on healthcare workers (Cabrera et al., 2015). A qualitative study on music and dance interventions in dementia care found that healthcare staff had increased positive interactions, relationships, communication, sense of confidence, empathy, and an improved understanding of residents’ emotional state and experience of limitations (Melhuish et al., 2016). Such aspects, together with the team cohesion, work engagement and job satisfaction, contribute to preventing stress and burnout of healthcare staff (Maslach and Leiter, 1999; Öhman et al., 2017; Costello et al., 2018). However, there are few music-based treatments targeted to care professionals and none, to the best of our knowledge, involving both dementia care professionals and older patients.

Thus, even if the practice and part of the scientific literature, confirm the power of music in improving OPDs’ functions and care professionals’ well-being at the work place, the quality of evidence is low and so further research is needed (Dyer et al., 2017).

Considering the above, further studies should include emotional well-being and social outcomes to improve the knowledge about the effects of music on older people with dementia and dementia care professionals to support the implementation of music interventions as a care strategy.

This protocol has been designed to cover this knowledge gap by testing an intervention based on active and passive music activities delivered in circle with older people with mild cognitive impairment and mild to moderate dementia, and dementia care professionals. Particularly, the study aims to investigate two principal factors: 1) the efficacy of the SOUND intervention on OPDs; and 2) the impact of implementing the SOUND intervention on the DCPs who are delivering it as a novel group. Overall, the pilot study aims to assess the feasibility and preliminary outcomes of the protocol. The study is part of the SOUND project, funded by the Erasmus + program (contract 2021-1-IT02-KA220-ADU-000033494) and aimed at designing an original music-based curriculum for dementia care professionals and testing a pilot music-based intervention with OPDs in Italy, Portugal and Romania. At the time of writing this manuscript, we were about ending the training for dementia care professionals and planning the intervention that will be concluded in the three countries in early 2024.

## 2 Materials and methods

### 2.1 Study design

The pilot study will adopt a mixed-method approach encompassing quantitative and qualitative analysis of data gathered from video recording and from psychometric and idiosyncratic tools during specific times of the trial (pre-post and longitudinal). This design was chosen in preparation of a future full-scale study that will be a non-randomized larger trial. The latter seems to be in line with the features of the intervention and with the target population. In fact, the intervention is based on the SOUND methodology that can be carried out in groups including seven or eight OPDs coupled by the same number of care professionals, according to the guidelines for music-based interventions for people with dementia recommending the involvement of few persons in every group for ensuring the effectiveness of the intervention (Janus et al., 2020).

Moreover, being aware that quantitative measures alone would not be able to fully capture the possible effect of a non-pharmacological treatment on older people with a degenerative disease such as dementia, the study design also included the collection of qualitative variables e.g., through biographies and live and *ex post* observations. This very time-consuming methodology would not be feasible in a randomized controlled trial that would pre-suppose a very large sample of subjects.

In light of the above, this pilot study, as well as the full-scale study, will adopt a sampling for meaning procedure (Luborsky and Rubinstein, 1995): people will be selected who can provide knowledge and meanings useful for understanding of individuals’ experience by taking the insider’s perspective. The latter is meaningful and informative, because has, in itself, individuals’ key symbols, values and ideas that shape and inform their experience with dementia in the role of professionals and older people with dementia (Luborsky and Rubinstein, 1995). Accordingly, the sample size considered the six sampling-based considerations by Onwuegbuzie and Collins (2017) for sampling by meaning.

This pilot study will also assess the feasibility of data collection methods and intervention implementation (recruitment, retention, intervention fidelity, acceptability, adherence to the intervention, and engagement) not only for the larger scale study but also in the view of the application of the intervention with people with more severe dementia or in rehabilitative units (Teresi et al., 2022). The feasibility assessment will be carried out by a senior researcher in the role of supervisor who will analyze the data collection method and the intervention implementation according to the guidelines provided by Teresi et al. (2022).

The study includes dementia care professionals (DCPs) (e.g., neuropsychologists, physicians, educators, nurses, professional caregivers), and older people with dementia (OPDs) that will be monitored in different phases, depending on the type of variable and instrument used. Some data will be analyzed by a pre-post group comparison. The data will be collected in three moments: one week before the start of the intervention (T0), at its end (T1), and 2 weeks after the end of the intervention (T2). Data will be also collected during the intervention phase and analyzed longitudinally depending on the time frame of the collection (daily from T0 to T2 versus at each SOUND session). The Figure 1 below shows the progression of the data collection and experimental phase within the Research design.

**FIGURE 1 F1:**
[figure not shown]
Research design.

### 2.2 Conditions

#### 2.2.1 Participants

In every study country, 15 OPDs and 15 DCPs will be recruited and participate to the experimentation, for a total of 45 OPDs and 45 DCPs (90 people overall). OPDs and DCPs’ inclusion and exclusion criteria are summarized below (Table 1).

**TABLE 1 T1:** Participants’ selection criteria.

Type of participants	Inclusion criteria	Exclusion criteria
OPDs	• Interest in the project and signed consent form • Age 65 + • To be able to see, hear and move • Diagnosis of MCI or dementia with mild to moderate impairment (MoCA total score ≥ 10/30) • Absence of aphasia (mild acceptable) • Be able to understand and undertake simple task as required during activities	•Lack of consent to participate • Age 65− • Not be able to see, hear and move even with the help of appropriate aids • Absence of formal diagnosis of MCI or dementia or severe level of impairment (MoCA total score ≤ 10/30) • Moderate to severe aphasia • Not able to understand and undertake simple task as required during activities
DCPs	• Having experience in the dementia field (e.g., educators, occupational therapists, physiotherapists, psychologist, sociologists, nurses, music therapists, professional caregivers, doctors) • Having interest in the project and signed consent form • For the (co-)facilitators and internal/external observers: having completed the SOUND training	• Lack of experience working in the dementia field • Lack of consent to participate • For the (co-)facilitators and internal/external observers: lack of completion of the SOUND training

Older people with dementias will be recruited from the study organizations, health care dementia services and community services such as diagnostic centers, dementia day care centers, residential care facilities and charities. Individuals will already have a formal diagnosis of MCI or dementia. Their level of cognitive impairment is routinely assessed by the health professionals of the organization to which they belong. Therefore, these health professionals will support the recruitment and selection processes. Ethical approval has been obtained depending on the national legal requirements. OPDs retention will be empowered by collaborating with their professional caregivers who will present the SOUND activities as a pleasant novelty and as a gift.

DCPs will be selected among those who have successfully completed the SOUND training i.e., a 22-h training based on an original SOUND curriculum^1^ co-designed with OPDs, DCPs and family caregivers in Summer 2022. The training was implemented in Spring 2023 in the three study countries, by means of an e-learning platform, called Virtual Music Circle (VMC), specifically developed within the SOUND project, and of face-to face lessons, to train the professionals who will be involved in the intervention. The SOUND training concept and learning outcomes are deepened in a dedicated paper (Quattrini et al., under review)^2^. The training was open to entire teams of participating organizations. Selected DCPs will include permanent staff and trainees who may or may not have an established relationship with OPDs. DCPs will be required to study OPDs biographies to properly relate to OPDs during the intervention considering their needs and characteristics. None of the selected DCPs used the SOUND intervention prior to the trial, therefore all of them will apply it for the first time. The total number of people per every SOUND activities group will be of about 15, including both OPDs and DCPs. For example, one group may include eight OPDs, five DCPs, the facilitator and the co-facilitator. The other group may be made of seven OPDs, four DCPs, the facilitator and the co-facilitator. This will be made to guarantee the correct delivery of the intervention and provide the conditions to enhance its potentials. In fact, small-sized units of 5–15 people can positively impact older people’s well-being, behavior, functioning, and activity engagement (Verbeek et al., 2009) and doing activities in small groups can hinder the participants’ cognitive decline (Kok et al., 2016) and favor social connection (Van Zadelhoff et al., 2011) more than in large groups.

An attendance sheet will be used to monitor participation, whereby absence from half or more of the sessions will result in a drop-out.

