#### 2.2.2 The SOUND intervention

The intervention will be implemented in Italy, in an Alzheimer day-care center, and in Portugal and Romania, in older people care facilities hosting people with dementia, where the DCPs who will be involved would regularly work. It includes 12 sessions delivered twice a week, for a 6-week period. Although there is no consensus regarding the frequency required for music-based interventions (Moreno-Morales et al., 2020), past research suggests that a higher occurrence may be more impactful (Carr et al., 2013).

During the intervention, OPDs and DCPs are positioned in a circle and everyone plays a specific role within the circle. OPDs will be the participants to whom the intervention is delivered. DCPs will implement the intervention by undertaking specific roles, i.e., the roles of facilitator, co-facilitator or internal observer. The role of facilitator will be assigned to a musician or a DCP with music skills, previously trained in the SOUND method. During the sessions, the facilitator proposes the activities to the participants in a responsorial style, holds the circle, welcomes and repeats any spontaneous and unexpected activity coming from the participants and proposes it to the whole circle. A DCP will be the co-facilitator, who is responsible for supporting the facilitator during the session. The role of internal observers, generally four per SOUND session, will be assigned to the rest of recruited DCPs: their task is to support the OPDs during the intervention in a non-intrusive and facilitating way while taking part in the activity. Facilitator, co-facilitator and internal observers take mental notes of their observations for reporting them in writing at the end of each session by using the live monitoring tools reported in Table 2. Four researchers (for covering all the sections of the circle circumference) will be the external observers: they will focus on OPDs’ emotional and behavioral responses to the proposed activities and take notes through dedicated tools (Table 2).

**TABLE 2 T2:** Live monitoring outcomes tools.

Target group	Tools	Variable	Point of view	When it is used
Dementia care professionals	Video recording	Behavior	Video camera (researcher)	During SOUND sessions
	Live Session Emotions Thermometer	Emotional state, behavioral reaction	Self-report	After each SOUND session
Older people with dementia	Video recording	Behavior	Video camera	During SOUND sessions

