The WHO Wellbeing Index (WHO-5) is a self-assessment tool to measure the subjective mental well-being of individuals which is validated for older people (Heun et al., 1999). It includes five items each scored from 0 to 5. The total score ranges from 0 to 25, with higher scores indicating greater mental well-being. Scores < 13 indicate poor well-being and suggest depression according to the criteria of the International Statistical Classification (Tiganov et al., 1997). It is recommended to transform the raw scores to percentage scores, by multiplying it by 4, for data analysis when investigating change over time (Topp et al., 2015). Low mood may be suggested by a percentage score of ≤ 50 whilst a score of ≤ 28 may indicates depression. Similar to Kikuchi et al. (2023), a variation of ± 10 points of the percentage score with 95% confidence intervals will be considered significant. The reliability and validity of the WHO-5 is well established (e.g., Bech, 2012; Takai et al., 2013). The WHO-5 will be the tool to assess the primary outcome for OPDs.

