#### 2.4 Data analysis

The analysis plan includes, for quantitative data, outcomes description. Normality in distribution of continuous variables will be assessed via Shapiro-Wilk test and the following measures will be reported: mean and standard deviation for normally distributed variables or median and interquartile range for non-normally distributed variables. Absolute frequency and percentage will be reported for categorical variables. Comparisons between outcomes and exposures will be made using the Chi Square test, (in the case of categorical variables) or *t*-test or F-Anova (in the case of comparisons between normally distributed continuous variables and the groups), or by non-parametric tests such as Wilcoxon rank-sum test or Kruskal-Wallis test (in the case of comparisons between non-normally distributed continuous variables and the groups). Through Pearson’s or Spearman’s correlation we are going to study the relationship between continuous variables as appropriate according to variables’ distribution. Temporal comparisons (T0 vs. T1, T0 vs. T2, or T1 vs. T2) will be conducted by *T*-test for paired samples. Possible multivariate models will be assumed in case of significant differences in outcomes at the univariate level: coefficients and standard errors or odds ratios and 95% confidence intervals will be reported according to the typology of outcomes (continuous or binary). Goodness of fit will be determined by R-squared of pseudo R-squared as appropriate. Subjects withdrawing from the study will not be replaced, according to the intention to treat (ITT) principle. Sequential imputation using chained equations method will be applied in case of missing values in covariates. Statistical analyses will be conducted by a statistician, who will be blind to group allocation prior to analysis. The significance threshold will always be set at p < 0.05. The software used for the analyses will be SPSS for Win V24.0 (SPSS Inc., Chicago, IL, USA).

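### Low attenders are classed as drop-outs, outcomes are not imputed and change is tested by paired t-test, which does not fit the intention-to-treat claim

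*Protocol article*

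**What the plan says.** Four statements in the protocol article bear on who is analysed.

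- **Drop-out rule (2.2.1 Participants).** Attendance is logged, and "absence from half or more of the sessions will result in a drop-out". Section 2.2.2 gives the denominator: "It includes 12 sessions delivered twice a week, for a 6-week period". The rule draws no distinction between older people with dementia (OPDs) and care professionals (DCPs).
- **Analysis principle (2.4 Data analysis).** "Subjects withdrawing from the study will not be replaced, according to the intention to treat (ITT) principle". This is the only mention of intention to treat.
- **Missing data (2.4).** "Sequential imputation using chained equations method will be applied in case of missing values in covariates". Missing outcomes are not mentioned.
- **Test of change (2.4).** "Temporal comparisons (T0 vs. T1, T0 vs. T2, or T1 vs. T2) will be conducted by" a paired t-test, and "The significance threshold will always be set at p < 0.05".

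Table 3 schedules WHO-5 (primary for OPDs) and BAT (primary for DCPs) at T0, T1 and T2. For WHO-5, section 2.3.2 adds that "a variation of ± 10 points of the percentage score with 95% confidence intervals will be considered significant". Section 2.1 lists retention and adherence among the feasibility outcomes.

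**The concern.** Attendance happens after baseline and may be related to the outcome. If low attenders leave the analysis, the before-after change describes those who stayed with the programme, not those who were enrolled. The article describes no control group, so change from T0 is the whole of the quantitative evidence on WHO-5 and BAT.

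The intention-to-treat label would then tell readers the opposite of what was done. Not replacing withdrawals is a recruitment rule; intention to treat concerns whose data are analysed.

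The consequences reach beyond feasibility. The Discussion sets 10-point expectations for WHO-5 and BAT, and section 2.5 says that evidence of effectiveness would bring the activities into the centres' routine. The people at risk of being lost are also those from whom a pilot learns most about acceptability.

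**Working it through.** The article gives no expected drop-out rate, standard deviation or power calculation, so it has no figure of its own to reproduce here beyond 15 × 3 = 45 per group, which is correct.

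**Step 1: the threshold.** Half of 12 is 6. Six or more absences make a drop-out, so those kept attended at least 12 − 6 + 1 = 7 sessions.

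**Step 2: following the rules in sequence.**

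1. A person who misses six sessions becomes a drop-out, even without having withdrawn and even if still available for assessment.
2. If drop-out has its ordinary meaning, that person has no T1 or T2 value.
3. A paired t-test omits anyone who lacks either value.
4. The stated imputation fills covariates. A paired t-test has none, so imputation cannot bring the person back.
5. The intention-to-treat sentence says only that the person is not replaced.

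The result is an analysis of those with at least seven sessions and both measurements.

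**Step 3: size on the WHO-5 percentage scale (illustration).** Assumptions: those kept gain 10 points, which is the plan's own threshold; drop-outs change by c; drop-out is about 10%, 20% or 30%, in whole people.

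All-enrolled mean = (n kept × 10 + n dropped × c) / 45

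| Kept / dropped | c = 0 | c = −5 |
|---|---|---|
| 40 / 5 | 400/45 = 8.9 | (400 − 25)/45 = 8.3 |
| 36 / 9 | 360/45 = 8.0 | (360 − 45)/45 = 7.0 |
| 31 / 14 | 310/45 = 6.9 | (310 − 70)/45 = 5.3 |

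The attenders-only analysis reports 10 in every row. The overstatement runs from 1.1 to 4.7 points.

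**Step 4: effect on the test when there is no true change.** Simulation with 20,000 runs per scenario, 45 enrolled, mean change 0 and a two-sided 5% test (the article does not state sidedness). The lowest attenders are removed, and attendance has correlation rho with outcome change.

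| Drop-out | rho = 0 | rho = 0.3 | rho = 0.5 |
|---|---|---|---|
| 10% | 5.0% | 7.1% | 10.7% |
| 20% | 5.2% | 9.7% | 19.4% |
| 30% | 4.8% | 13.5% | 30.8% |

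For rho of 0.3 to 0.5 the mean change is shifted upwards by 0.06 to 0.25 SD. Analysing all 45 keeps rejection at 4.9% to 5.1% in every scenario. With rho = 0 there is no distortion.

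**The case against.** The strongest reply is that the article never says that drop-outs go unassessed or leave the t-tests. Table 3 sets no attendance condition. One can read the drop-out label as serving only the retention and adherence counts, with intention to treat governing the analysis. A reader might infer that exclusion of low attenders is a stated rule. The documents do not support that; it is an inference from the ordinary meaning of the word. It still leaves something to correct, because under the benign reading the wording of 2.2.1 misleads, and a site could stop collecting T1 and T2 data on that basis.

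A reader might also infer that the WHO-5 gain is bound to be inflated and the BAT score bound to fall too far. The documents do not support that either. Absence could reflect illness, transport or shift rotas, and if it is unrelated to outcome there is no bias.

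Nor is covariate imputation pointless. Section 2.4 foresees multivariate models where univariate differences are significant, and it has a use there. It simply does not help the paired comparisons.

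Finally, analysis sets and missing-outcome methods are often left to an analysis plan, and their absence alone would be no finding. This point rests on something else: the article chose to state a drop-out rule, a principle, an imputation scope and a test, and these do not fit together. That the study is a pilot lowers the stakes without removing the conflict.

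**Conclusion.** The point holds as a conflict among stated rules. Taken literally, they lead to an analysis of people who attended at least seven of 12 sessions, under an intention-to-treat label that is attached to the wrong idea. One step, that drop-outs have no later assessment or are left out, is inferred.

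The size cannot be determined from the document. Under the assumptions shown, a 10-point gain in attenders corresponds to 5.3 to 8.9 points over all enrolled, with 8.0 at 20% drop-out and no change in drop-outs. The inflation of the test depends wholly on an assumed link between attendance and outcome. An overstated benefit is plausible but not established.

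This should be fixed, though it does not invalidate the pilot; confidence is medium.

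**What to change.** - In 2.2.1, record attendance below the threshold as non-adherence, a feasibility outcome, and not as drop-out.
- State that T1 and T2 assessments continue for everyone enrolled, whatever their attendance, unless consent is withdrawn.
- In 2.4, define the primary analysis set as all enrolled OPDs (and, separately, DCPs) with a T0 value, regardless of attendance.
- Name a method that handles missing outcomes. A mixed model for repeated measures over T0, T1 and T2 is one acceptable choice; multiple imputation that includes the outcomes is another.
- Report the set that attended more than half the sessions as a sensitivity analysis only.
- Remove the intention-to-treat phrase from the non-replacement sentence.

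This concerns data collection and analysis, not who goes on attending sessions. The cost is wording in two sections, a few extra T1 and T2 assessments and a possibly less favourable estimate. No additional participants are needed. Assessments not made at T1 and T2 cannot be recovered later, so the follow-up wording matters most.
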